## Abstract

**Background:**

Worldwide prevalence of generalized anxiety disorder (GAD) is considered high; in Europe lifetime prevalence has been estimated at 4.3 to 5.9%. High levels of anxiety disorders have been reported in university students, affecting 25 to 30% of the population. Young adults are some of the most vulnerable for the onset of mental health disorders and any stressors may act as a catalyst for their onset. The absence of resources can often mean that many do not seek treatment. Other factors that impede access to resources include such things as a lack of trained professionals, personal stigma, and waiting lists. Anxiety disorders can be treated successfully; indeed brief forms of cognitive-behavior therapy have been recommended. One potential avenue for research and development is that of delivering low-intensity interventions online for students with GAD. Therefore, the current study seeks to investigate the potential effectiveness for a low-intensity online CBT-based treatment for GAD in a service-based setting; implemented as one step in a stepped-care model.

**Methods/Design:**

The research is a service-based effectiveness study utilizing a randomized waiting-list controlled design. The active intervention consists of six weekly modules of online CBT. Participants are assigned a supporter who provides weekly post-session feedback on progress and exercises. Participants will complete the GAD-7 as the primary outcome measure. Secondary outcomes include pathological worry, depression and measures of well-being. At three-months follow-up data will be collected using the GAD-7, BDI-II, PSWQ, ED-Q5 and WSAS. Post-session data will be collected on significant in-session events in treatment (HAT). A satisfaction with treatment measure will be administered post-treatment (SAT).

**Discussion:**

The study will be a contribution to the potential for a low-intensity internet-delivered program implemented in a service-based setting; implemented as one step in a stepped-care model. The study will be a contribution to the already established work in online treatments for anxiety worldwide. The study will assess the utility of an innovative digital health solution (SilverCloud) to deliver such interventions.

**Trial registration:**

Current Controlled Trials ISRCTN16303842.

## Background

Anxiety disorders rank high among the most common mental health disorders worldwide [1]. Anxiety disorders include generalized anxiety disorder (GAD), panic disorder and agoraphobia (PD/A), panic attacks (PA), specific phobia (SP), and social anxiety disorder (SAD) [2]. In general, anxiety is characterized by excessive worry about everyday events, irrespective of whether they are internal or external or originating in the past, present or future [2]. In Europe, 12-month prevalence of anxiety disorders has been estimated at 14% [3-5].

GAD is typically considered a chronic condition; a homogenous disorder characterized by excessive worry affecting several domains including restlessness, fatigue, difficulties concentrating, muscle tension, sleep disturbances, and irritability [6]. In Europe the lifetime prevalence of GAD has been estimated at 4.3 to 5.9%, with a 12-month prevalence of 1.2 to 1.9%, yet only a very small percentage seek treatment [7]. GAD, like other mental health disorders, often presents with comorbidity - principally mood disorders or other types of anxiety disorder [4,8]. GAD is associated with significant deleterious effects: economic, personal, intrapersonal and societal [9,10], which can cause significant impairment and reduced quality of life for an individual and their family [11].

### Anxiety and students

Several studies have reported elevated levels of anxiety and stress in university students [12]. The prevalence of anxiety in high school and university students has been reported to be between 25 and 30%, in response to their academic demands [13,14]. Academic stress is highly prevalent and it can contribute significantly to anxiety and depression among college students. For instance, a recent survey of young adult students in Ireland using the Depression Anxiety Stress Scale (DASS-21) [15], showed levels of clinical anxiety at 36% (8% in the mild range, 15% in the moderate range, 5% in the severe and a further 9% in the very severe range) and 30% with clinical symptoms of stress (10% in the mild range, 10% in the moderate range and 10% in the severe (7%) to very severe (3%) range) [16].

The transition to university and the management of the resulting academic demands can be a stressful time for many students. The majority of students are at a developmental stage where the onset of mental health difficulties can arise and any stressors may act as a catalyst for their onset [12,17,18]. Indeed, young adults aged between 17 and 25 are at high risk of developing a serious mental illness such as an anxiety disorder, and whilst sometimes mental disorders can be difficult to diagnose early on, the risk of delayed diagnosis is often associated with treatment resistance and poorer longer-term outcomes [12]. The result of a lack of opportunity for early diagnosis and treatment can often mean academic failure and dropping out of university. Furthermore, any such underachievement or failure can have long-term consequences on self-esteem and progress in future life [12].

Since the publication of the Royal College of Psychiatrists updated report (2011) on the mental health of students at university, there is no evidence of the abating of the concerns that were previously raised [18] he demand for counseling and mental health services among students has only increased [12]. This is due to a broad range of factors, including the rise of family breakdowns, the increase in student monetary contributions to university, the changing demographic of the student population (with a greater diversity of international students), and the case that many students now have to work to survive, places an increased demand not only on their time but also their mental health and wellbeing [12].

### Treating anxiety disorders

Anxiety can be treated successfully through disorder specific treatment plans or treatments that target common elements and symptoms across anxiety disorders [19,20]. Treatments for GAD include pharmacological and psychological and both have demonstrated their efficacy [21]. By far the most extensively researched psychological treatment for GAD is cognitive-behavior therapy (CBT) which has been shown to be a highly effective treatment for GAD [22]. Different cognitive and behavioral techniques compose any treatment for GAD. They can include cognitive restructuring, behavioral exposure, worry exposure (staying with feared outcomes), relaxation training, and problem solving, among others. CBT for GAD aims to help the user overcome emotional avoidance and learn that their anxiety is not debilitating, but can be managed and indeed recede over time [23-25].

To date a number of theoretical models have been proposed for GAD [26]. Perhaps the most well-defined and empirically supported of these are the Avoidance Model of Worry and GAD (AMW) [27] and the Intolerance of Uncertainty Model (IUM) [28]. Both have gathered supporting empirical evidence for their central constructs and have developed and researched treatment protocols based on their model [26]. The IUM is largely a cognitive model explaining the pathogenesis of GAD, whereas the AMW is an integrated model that includes cognitive alongside emotional and behavioral components. The treatment protocol used in this study is largely based on the AMW model of GAD.

It is the case that many with anxiety disorders have no diagnosis nor seek treatment [29,30]. Consequently, mental health disorders such as anxiety disorders often go undetected, especially where accessing psychological services is difficult and/or services are overburdened, as is the case for many university institutions [12,31]. Additional barriers to accessing treatment exist, such as a lack of available trained professionals, waiting lists, lack of motivation for change, negative perception of psychological treatments, indirect costs of treatment (and direct costs in some cases), personal difficulty such as stigma, and low mental health literacy. Each of this barriers can play an important role in choosing whether or not to seek diagnosis and treatment [32,33].

CBT as a brief psychological interventions has demonstrated its efficacy and has the potential to significantly reduce the burden of anxiety disorders [34]. CBT is highly suitable to being delivered as a low-intensity intervention within a model of stepped-care [35]. Ireland is far behind its European neighbors in developing and implementing stepped-care models for mental health service delivery that involve both low-intensity (such as bibliotherapy) and high-intensity (such as face-to-face therapy) interventions, despite it being recommended as best practice [36] and its demonstrated success to date [37].

### Stepped-care model of treatment

The central idea in developing stepped-care models in mental health is to extend access [38]. In recent years attempts to overcome barriers to access have been addressed through the development and implementation of a wide range of low-intensity interventions including internet-delivered treatment programs. Programs have been developed and employed in the treatment of a range of disorders and their results support their efficacy [39-42]. Internet-delivered treatments for anxiety disorders have included interventions for panic disorder, SAD, SP, and posttraumatic stress and they have established findings that support their potential effectiveness and efficacy [43-47].

More precisely, a number of studies have investigated the potential for internet-delivered treatments for GAD and they have reported significant post-treatment and follow-up gains [33,48-51] similar to those found in face-to-face treatment studies [52]. A recent meta-analysis of internet-delivered treatments for GAD demonstrated large post-treatment effects for GAD symptoms (*d* = 0.91) and pathological worry (*d* = 0.73) in favor of the active interventions when compared to waiting list control groups [53]. In addition, online studies for anxiety treatment that provide human support yield enhanced results when compared to those with no human support [54]. The demand for psychological treatments will never be met from high-intensity therapy, therefore internet-delivered treatments are a valuable alternative.

### Delivering online low-intensity interventions for GAD

The internet offers the possibility of delivering a treatment intervention at low cost and perhaps overcoming some of the barriers to access mentioned earlier. Online technologies can deliver treatment incrementally and in an engaging way. Furthermore, internet penetration in Ireland is at 76.8% [55] and it is likely that it is an attractive medium, especially for younger people as they are already high users of the internet and related tools. In a recent Irish survey that asked a student sample about the places they were likely to use as a source of support, the internet was the highest scoring answer at 78%, above friends, parents, doctors, or other professionals [16].

Some previous research has assessed the relevance of low-intensity internet-delivered treatments for anxiety disorders in service-based settings [56-58]. However, only a handful of studies have investigated the efficacy and effectiveness of low-intensity internet-delivered treatments for GAD [33,48-51]. The current study seeks to make a contribution towards understanding the relevance of a low-intensity internet-delivered treatment for GAD in a service-based setting in Ireland.

Therefore, using established CBT principles informing skills and strategies for the management of GAD in an integrated disorder-specific treatment plan, the study aims to deploy these using a novel digital health software platform (SilverCloud SilverCloudHealth Ltd., [name].) that integrates a number of innovative engagement strategies for improving the user experience: personal, interactive, supportive, and social [59]. The details of the platform and the content of treatment are described in more detail below.

### Dropout from online treatments

A problem that has faced online treatments in general, and more particularly self-administered treatments without support, is that of dropout [60]. Dropout is a continued cause of concern as it is suggested that completing the entire course will benefit users, although several online studies have reported benefits for users who have not completed the entire course of treatment [61]. Some studies have collected information regarding dropout, suggesting difficulties using the computer, negative features of the program, perceiving the course as too demanding, poor clinical progress, receiving alternative treatment, feeling better, lack of time, and problems understanding the computer program [42,62]. The technology used in the current study has been specifically designed to include a number of engagement strategies for improving the user experience: personal, interactive, supportive, and social. An investigation of dropout will be valuable in assessing the user’s experience of online delivery.

### Objectives of the trial

The study aims to implement and evaluate the effectiveness of a low-intensity online self-administered treatment for anxiety (with support) for students with GAD symptoms. There are four research questions. Firstly, can an online treatment for GAD symptoms be effective for an adult student population in a service-based setting? Secondly, what do participants find helpful and hindering in their online treatment for GAD symptoms? Thirdly, are participants satisfied with accessing and using an online treatment? Fourth and finally, what are the reasons for dropout from an online treatment?

Based on the success that has been achieved with supported online treatments in general [42,54,63,64] and with internet-delivered interventions for GAD [33,48-51,65], we hypothesize that participants in the trial will demonstrate significant decreases in GAD symptoms post-intervention and a corresponding positive change in pathological worry and quality of life.

## Methods/Design

### Study design

The research is a service-based effectiveness study utilizing a randomized controlled trial design of an internet intervention for the treatment of GAD symptoms. Participants will be randomized into two groups: the internet-delivered intervention with clinical support and a waiting list control group. The study protocol, information on the study, informed consent and related materials received ethical approval from the School of Psychology, Trinity College Dublin (22 November 2013).

### Sample size

Previous studies of online interventions for GAD that have used a CBT protocol similar to the intervention in the current study have reported post-treatment effect sizes of between 0.79 and 1.67, and follow-up effects of between 0.69 and 1.65, based on sample sizes ranging from 10 to 97 [33,48-50]. We calculated power using G-Power software [66]. Using a power of 0.80 and an alpha of 0.05, we would need 50 subjects in each arm of the trial to observe a moderate (*d* = 0.50) post-treatment difference on the main outcomes.

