### Planned statistical analysis

The analyses will be based on the intention-to-treat principle, including those who began treatment and provided follow-up data irrespective of treatment compliance. Missing data will be handled using Last Observation Carried Forward (LOCF). Effects will be tested at the 0.05 level. Analysis of variance (ANOVA)will be used to investigate any baseline demographic or clinical differences between the groups.

To test the main hypotheses, repeated measures ANOVA will be performed for the primary outcome measure for anxiety (GAD-7). Thereafter ANOVAs will be executed for the BDI-II, PSWQ, EQ-5D and WSAS. Contrasts will be conducted comparing changes from baseline to post-treatment for each group separately. Further analysis of baseline demographic variables and any relation to outcomes will be conducted. Effect sizes (Cohen’s d) will be calculated both within and between groups, based on the pooled standard deviation. For Cohen's d an effect size of 0.2 to 0.3 can be considered a small effect, around 0.5 a medium effect, and 0.8 upwards a large effect [83].

Analysis will be made to determine the proportion of participants who make a clinically meaningful change at the end of treatment and at follow-up. Pre-treatment, post-treatment, and follow-up GAD-7, BDI-II and PSWQ scores will be compared with clinical cutoffs to provide an indicator of remission. Remission is defined as the number of participants who initially scored at or above the established clinical cutoffs, and then at post-treatment and follow-up scored below the established clinical cutoffs: GAD-7 total score <10 [67]; BDI-II total score <14 [84], PSWQ <45 [85], and WSAS <10 [79]. In addition, we will calculate the relative risk of anxiety and depression by dividing the event rate (anxiety or depression) post-treatment by the event rate pre-treatment [70]. An estimation of recovery will be made by identifying the number of participants in each group who demonstrated a reduction of 50% of pre-treatment GAD-7, BDI-II and PSWQ scores [70]. In addition we will also calculate the number of reliably changed and recovered participants using Jacobson and Truax’s [86] criteria.

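### The stated 80% power with 50 per arm matches an undeclared one-sided test; a two-sided comparison at d = 0.50 has about 70%

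*Protocol article*

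**What the plan says.** The Sample size section of the protocol article gives the planning inputs as "Using a power of 0.80 and an alpha of 0.05" and concludes that "we would need 50 subjects in each arm of the trial to observe a moderate" effect, defined as a post-treatment difference of d = 0.50. It names the software ("We calculated power using G-Power software [66"]) but not the test family, and it does not say whether the alpha is one- or two-sided. It also cites earlier trials with effects of 0.79 to 1.67 after treatment and 0.69 to 1.65 at follow-up.

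The Planned statistical analysis section says "Effects will be tested at the 0.05 level" and that "repeated measures ANOVA will be performed for the primary outcome measure for anxiety (GAD-7"). It adds "Missing data will be handled using Last Observation Carried Forward (LOCF"). No section mentions a one-sided test. Under Assessments, both arms are measured at baseline and week six, and only the active arm at the later follow-up. The between-arm comparison therefore rests on two time points.

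**The concern.** The familiar result for two equal groups, d = 0.50, two-sided alpha 0.05 and 80% power is 64 per arm. A stated 50 per arm is 14 short in each arm, 28 in total. Either the calculation was made for a test other than the one that will be run, or it used an input that is not reported.

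The protocol chose d = 0.50 as the effect it wants to be able to detect and attached a probability of 0.80 to that. If the real probability is nearer 0.70, the chance of missing a true moderate effect is about 30%, not 20%. A non-significant result would then carry less weight against a moderate effect than the protocol implies.

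**Working it through.** **Inputs from the protocol article.** d = 0.50, alpha 0.05, power 0.80, n = 50 per arm (Sample size); repeated measures ANOVA, effects tested at 0.05 (Planned statistical analysis).

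**Input not in the documents.** The pre-post correlation r of the outcome. It is assumed below over 0.3 to 0.7, with equal standard deviations at baseline and week six.

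**1. Reproducing the stated 50.** The normal approximation is n per arm = 2(z_alpha + z_power)² / d².

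- One-sided: 2 × (1.645 + 0.842)² / 0.25 = 49.5, so 50. The non-central t gives 50.15, so 51, with power 0.799 at n = 50.
- Two-sided: 2 × (1.960 + 0.842)² / 0.25 = 62.8, so 63. The non-central t gives 63.77, so 64.

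The stated figure matches the one-sided calculation and not the two-sided one.

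**2. Two-sided power at 50 per arm.** The noncentrality is d√(n/2) = 0.50 × √25 = 2.5. The normal approximation gives Φ(2.5 − 1.960) = Φ(0.54) = 0.705, and the non-central t gives 0.697. The effect detectable with 80% power at 50 per arm is d = 0.566.

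**3. Sidedness of the planned test.** With two arms and two time points, the group-by-time F test has one numerator degree of freedom and equals the square of the t statistic comparing mean change between arms. Rejecting at the 0.05 level of F is the same as a two-sided t test at 0.05. A one-sided 0.05 test would correspond to F at the 0.10 level, which is not what the analysis section says.

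**4. Power of the planned test.** For the group-by-time test the effective standardised effect is 0.50 / √(2(1 − r)). For a baseline-adjusted ANCOVA it is 0.50 / √(1 − r²). Two-sided power with 50 per arm:

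| Assumed r | Group-by-time | ANCOVA |
|---|---|---|
| 0.3 | 0.553 | 0.737 |
| 0.4 | 0.618 | 0.771 |
| 0.5 | 0.697 | 0.816 |
| 0.6 | 0.790 | 0.872 |
| 0.7 | 0.892 | 0.934 |

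The group-by-time test reaches 80% when 0.50 / √(2(1 − r)) = 0.566. This gives 2(1 − r) = (0.50/0.566)² = 0.78, so r is about 0.61.

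**5. Power at the effects the protocol cites.** A two-sided post-score comparison with 50 per arm has power 0.927 at d = 0.69 and 0.974 at d = 0.79.

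**The case against.** The strongest defence is that the calculation is coherent as it stands. The Sample size section never says two-sided, the figure reproduces one-sided, and the hypothesis under Objectives of the trial is directional: symptoms are expected to fall. This stands to the extent that the defect should not be called an arithmetic error. It does not settle the matter, because a directional hypothesis is not a declaration of a one-sided test, and the analysis that is declared is non-directional.

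Second, 70% is not the power of the planned primary analysis. This also stands. Step 4 shows that the group-by-time test may fall below or above 80%, depending on a correlation the documents do not give. A reader might infer that the trial flatly lacks its stated power. The documents do not support that for the test to be run; they show only that the stated 80% cannot be recovered for it from the inputs given.

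Third, a reader might add a dropout penalty, since the background section says "Dropout is a continued cause of concern". That sentence concerns finishing the treatment course, not missing week-six outcomes. The documents give no expected rate of missing outcomes, LOCF fills missing values and does not delete them, and a condensed article may leave an allowance to the full protocol. Under an assumed 20% or 30% loss analysed as complete cases, two-sided power would be 0.598 or 0.541. Those figures are illustrations and do not describe this plan.

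Fourth, one could guess at other software settings that return about 100 in total, such as a repeated-measures between-subjects main effect. Nothing in the documents indicates that this was done, so neither the origin of the figure nor a criticism of it can rest there.

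Finally, d = 0.50 is well below the cited earlier effects, so the practical risk is limited if those effects hold. This stands and bears on the weight of the point, but not on the accuracy of the figure.

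**Conclusion.** The concern holds in a limited form. The pairing of 50 per arm, alpha 0.05, 80% power and d = 0.50 is reproduced from the stated inputs only by a one-sided test, which is declared nowhere and does not match the ANOVA planned at the 0.05 level. For a two-sided comparison of post-treatment scores, power is 0.697, the required size is 64 per arm, and the effect detectable with 80% power is about 0.57.

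These figures are exact for a two-sample t test with complete data. Those for the group-by-time test and ANCOVA also rest on an assumed correlation and on equal standard deviations at the two times. The second assumption is uncertain because entry requires a GAD-7 score of at least 10, which restricts the baseline range. That the original calculation was one-sided is an inference from the match. What is established is that the sample-size statement and the analysis section do not describe the same test.

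**What to change.** Keep 50 per arm. State the test and its sidedness, name GAD-7 as the outcome to which the calculation applies, and replace the power sentence. Either of these would do:

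- *With 50 per arm, a two-sided 0.05 test of the post-treatment difference in GAD-7 has about 70% power for d = 0.50 and 80% power for d = 0.57, before any missing data.*
- A statement based on the planned group-by-time test, or on a baseline-adjusted ANCOVA, with the assumed pre-post correlation given and justified. At a correlation of 0.5, ANCOVA with 50 per arm has about 82% power before missing data, whereas the group-by-time test has about 70%. Choosing ANCOVA would also mean changing the analysis section, which does not now name it.

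If a figure allowing for dropout is added, label the rate as an assumption and say how it relates to the handling of missing data.

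The cost is one paragraph and, under the first option, a less favourable stated power. No additional participants are needed. The text can still say that effects of the size seen in the cited earlier studies (0.69 and above) would be detected with over 90% power.
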